**Methods:**

This is a 13-week randomized, double-blind, placebo-controlled study. Patients will be randomized to either a mixture of a complex blend of EAA and intermediates of the tricarboxylic acid (TCA) cycle (citrate, malate, succinate) supplementation (or placebo) upon admission at the intensive residential and day-hospital treatment for eating disorders. Ninety-two participants with AN aged 16–50 years will be recruited from a specialized intensive treatment of eating disorders. Double-blind assessment will be conducted at baseline (T0) and the end of the 13 weeks of treatment (T1). The study’s primary aim is to evaluate the efficacy of supplementation with EAA and TCA intermediates on the change in lean body mass (LBM) with weight restoration in patients with AN who are undergoing specialist treatment for eating disorders. The secondary aims of the study are to assess the effect of dietary supplementation on physical fitness, weight restoration, modification of AN and general psychopathology, and psychosocial impairment.

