### Sample size {14}

Since this is an efficacy study, the primary data evaluation will be the analysis of completers. The primary outcome of interest is the percentage increase in the patient’s LBM with weight recovery at the end of the intensive treatment. The sample size was determined based on the difference between the intervention group and the control group on the change in LBM between baseline and end of treatment. We hypothesized, referring to the data of our previous study [27], that the control group could have an 8.8% increase in LBM, while the intervention group could have a further 2% increase in LBM [48, 49] to reach a variation of LBM of 10.8%. The standard deviation assumed for the sample size calculation is 3.2%.

Based on these premises, will be necessary to have a group of completers of 80 patients at the end of the treatment (i.e., 40 patients per treatment condition). To calculate the initial sample needed to generate 80 patients at the end of treatment, we considered the intervention interruption rate (set at 15%). This calculation results from an initial sample of 92 patients (46 per treatment condition).

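### Randomising 92 with 15% loss gives about 78 completers, not the 80 the sample size section requires

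*Protocol article*

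**What the plan says.** All the relevant figures are in the Sample size section of the protocol article.

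- Analysis that the sample size serves: "the primary data evaluation will be the analysis of completers".
- Completers required: "will be necessary to have a group of completers of 80 patients at the end of the treatment (i.e., 40 patients per treatment condition").
- Allowance for loss: "we considered the intervention interruption rate (set at 15"%).
- Purpose of the allowance: "To calculate the initial sample needed to generate 80 patients at the end of treatment".
- Result: "This calculation results from an initial sample of 92 patients (46 per treatment condition").

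The Methods paragraph of the abstract repeats the target: "Ninety-two participants with AN aged 16–50 years will be recruited". The inflation formula is not written out, and neither the significance level nor the power is given for the calculation.

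**The concern.** An interruption rate is a fraction of the patients who start. To finish with a given number, that number has to be divided by the fraction expected to remain. Adding 15% to the final number gives too small a sample, because the 15% is later lost from the larger starting group. The printed 92 is what the second method produces.

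What is at stake is whether the planned sample delivers the number that the protocol itself calls necessary for its primary analysis. That analysis is of completers, so the completer count sets its power.

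**Working it through.** **Inputs, all from the Sample size section**

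- Completers needed: 80 (40 per arm)
- Interruption rate: 15%
- Stated initial sample: 92 (46 per arm)
- Difference in LBM increase: 2 percentage points (8.8% against 10.8%)
- SD: 3.2%

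**Step 1. Reproduce the plan's 92.**

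- Completers × (1 + loss): 80 × 1.15 = 92.0, and per arm 40 × 1.15 = 46.0. Both match exactly.
- Completers / (1 − loss): 80 / 0.85 = 94.1. This does not give 92.

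**Step 2. What 92 delivers at the stated loss.**

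- 92 × 0.85 = 78.2 completers, or 46 × 0.85 = 39.1 per arm.
- Shortfall: 80 − 78.2 = 1.8 completers.
- Loss at which 92 would yield 80: 1 − 80/92 = 13.0%.

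**Step 3. What 80 completers at 15% loss requires.**

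- 80 / 0.85 = 94.1, rounded up to 95.
- Per arm: 40 / 0.85 = 47.06, rounded up to 48, so 96 in equal arms.

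**Step 4. Chance of at least 80 completers if each patient independently completes with probability 0.85 (binomial).**

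| Randomised | Expected completers | P(at least 80) |
|---|---|---|
| 92 | 78.2 | 0.363 |
| 95 | 80.75 | 0.651 |
| 96 | 81.6 | 0.733 |

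**Step 5. Effect on power.** Alpha and power are not stated, so this step rests on an assumption. With two-sided 5% and 80% power, the normal approximation gives

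n per arm = 2 × (1.960 + 0.842)² × 3.2² / 2² ≈ 40.2,

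which is close enough to the plan's 40 to make two-sided 5% the natural reading. One-sided 5% is shown as the alternative. With standardised difference 2/3.2 = 0.625, the independent-samples t-test has the following power:

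| Completers per arm | Two-sided 5% | One-sided 5% |
|---|---|---|
| 40 | 78.8% | 87.0% |
| 39 | 77.8% | 86.2% |

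Either way, the loss is about one percentage point.

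**The case against.** The strongest reply is that the error is real but has little consequence. It is worth less than one completer per arm and about one point of power, and no conclusion of the trial would turn on it. That is right, and it limits how much weight the point should carry.

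Other parts of the defence stand as qualifications:

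- The 36% chance of reaching 80 should not be read alone. A correctly inflated sample of 95 or 96 would still miss 80 about 35% or 27% of the time, because dividing by 0.85 fixes only the expected number.
- Under two-sided 5%, power is already below 80% at 40 per arm; the t-test would need 42 per arm. The dropout arithmetic does not cause that gap. Under one-sided 5% there is no gap.
- Multiplication by 1.15 is inferred from an exact match and is not documented.

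One argument does not stand. The Statistical methods sections add mixed models, an intention-to-treat set and multiple imputation, so dropouts are not discarded everywhere. But the Sample size section names the completer analysis as the primary evaluation and sizes the trial for it. The other analyses do not raise the number of completers.

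Nor is this a matter of condensation in a journal article. The target, the loss rate and the resulting sample are all printed, and they disagree. Rounding does not explain it either, since 94.1 does not round to 92.

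**Conclusion.** The concern holds. At the protocol's own 15% interruption rate, 92 randomised patients are expected to give 78 completers, about 39 per arm, and not the 80 stated as necessary. The sample is three short of the required total, or four short with equal arms. This rests only on figures printed in the Sample size section and needs no assumption about alpha or power.

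The statement that the shortfall costs about one point of power rests on the stated difference and SD together with an assumed 5% level. It changes little between one-sided and two-sided testing. This is a false figure in the sample size statement for the primary analysis, with a small practical effect.

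**What to change.** Correct the Sample size section in one of these ways.

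1. **Keep 92 and restate the yield.** Say that 15% interruption leaves about 78 completers (39 per arm), with about 78% power for a difference of 2 and SD of 3.2 at two-sided 5%, if that is the intended level. State the level in the same sentence.
2. **Keep 92 and 80 and restate the loss.** Say that 92 yields 80 completers only if interruption does not exceed 13%. This is suitable only if the team can support a rate below its present 15%.
3. **Keep 80 completers and 15%.** Change the initial sample to 96 (48 per arm), here and in the abstract.

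Options 1 and 2 cost nothing in patients or time; option 1 reports a slightly less favourable figure. Option 3 adds four patients. The Recruitment section gives about 70 adult admissions with AN per year and the Trial status section gives 18 months of enrolment, so about 70 × 1.5 = 105 adult admissions. Ninety-six would be 96/105 = 91% of these, against 92/105 = 88% now (eligible patients aged 16 and 17 are not in that count). Given how small the effect on power is, option 1 is the simplest.

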### Recruitment {15}

The Department of Eating and Weight Disorder of Villa Garda Hospital accepts about 70 adult patients with AN per year. All the patients are referrals from their family doctors.

Study participants will be recruited among patients who meet the diagnostic criteria for AN, assessed with the EDE.17 interview [35, 36] consecutively admitted at the inpatient or day-hospital rehabilitative of the Department of Eating and Weight Disorder of Villa Garda Hospital.

On the day of admission into the Unit, the patient will meet the ward physician to collect the medical history, the physical examination, and the prescription for humoral and instrumental analyses. On this occasion, the enrollment phase will take place, including the complete data collection for the compilation of the data collection form. At the end of the data collection, if the criteria for inclusion in the study are met, the patient will receive detailed information on the following:Study procedures and objectives.Purposes, methods, inconveniences, risks, and benefits that the study may entail.Freedom to participate and withdraw from the study without affecting subsequent treatment.Compensation procedures and treatment of any damages deriving from participation in the study.

Before requesting to sign the informed consent and the possibility of using (and having permission to use) the information collected during the study, the patient will be asked to read an information sheet containing detailed information on the study.

If the patient or, in the case of a minor patient, his parents and/or legal guardians agree to participate in the study, they will have to sign the informed consent form and the authorization to process personal and sensitive data.

Supposing that the patient meets the criteria for inclusion in the study but refuses to participate, she will continue the intensive treatment at the Department of Eating and Weight Disorder of Villa Garda Hospital.

After the interview and signing of the informed consent and data processing, the patient will be randomized to AmT-P or placebo supplementation. Both arms will receive the same intensive treatment for the eating disorder.

At the end of the interview with the patient, a letter will be sent to the family doctor, giving information on the study that the patient will address.

### Concealment mechanism {16b}

Use of a validated password website will ensure concealment.

### Implementation {16c}

The trial sponsor and the principal investigator team will generate randomization with the allocation sequence.

## Assignment of interventions: blinding

### Who will be blinded {17a}

Blinding will be accomplished through multiple methods. Trained staff uninvolved in trial operations or analyses will produce a group code, receive and label product bottles accordingly, and generate stratified randomization sequences using freely available software. Upon randomization, participants will be assigned a new alphanumeric ID reflecting their enrollment status. All parties involved in trial conduct will remain blinded until the primary trial analyses are deemed complete by all trialists.

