### Trial design {8}

This study is a randomized, double-blind, placebo-controlled superiority trial. Patients will be randomized to either AmT-P or placebo supplementation upon admission to the treatment. Randomization is carried out at the hospital entry by adopting a stratification for the following parameters: (i) age (16–50); and (ii) body mass index (BMI) (BMI > 14 kg/m^2^). The treatment lasts 13 weeks.

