## Methods: participants, interventions, and outcomes

### Study setting {9}

The study will be performed at the Department of Eating and Weight Disorder of the Villa Garda Hospital (Garda, Italy), a community clinic accredited with the Italian National Health System for the inpatient and day-hospital rehabilitation treatment of eating disorders.

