### Strategies to improve adherence to interventions {11c}

Adherence will be monitored daily throughout the trial, as the sachets of the placebo and the EAA supplementation will be administered by the team nurse and taken by the participants in front of them. Participants will be considered adherent by taking > 80% of expected doses throughout their participation in the trial. The study product will be stored in a locked cabinet in a locked room for future quality assessment.

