### Procedure for unblinding if needed {17b}

Unblinding will be permissible only in the case of a severe adverse event requiring hospitalization or resulting in a fatality.

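### Product is labelled by group code and not by participant, so one permitted unblinding can disclose the allocation of every participant sharing that code

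*Protocol article*

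**What the plan says.** All references are to the protocol article.

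- **Labelling.** Under Who will be blinded {17a}, staff outside trial operations and analyses "will produce a group code, receive and label product bottles accordingly".
- **Participant identifier.** The same section says that "participants will be assigned a new alphanumeric ID reflecting their enrollment status". It does not say that the product carries this ID or any other participant-specific number.
- **Promise.** It ends: "All parties involved in trial conduct will remain blinded until the primary trial analyses are deemed complete by all trialists".
- **Unblinding.** Procedure for unblinding if needed {17b} reads: "Unblinding will be permissible only in the case of a severe adverse event requiring hospitalization or resulting in a fatality". It describes no means of opening one participant's allocation alone.
- **Arms and site.** Trial design {8}: "Patients will be randomized to either AmT-P or placebo supplementation upon admission to the treatment". Study setting {9}: "The study will be performed at the Department of Eating and Weight Disorder of the Villa Garda Hospital".
- **Handling.** Under Strategies to improve adherence {11c}, the sachets "will be administered by the team nurse and taken by the participants in front of them".
- **Presentation.** Intervention description {11a} has sachets stored in boxes, whereas {17a} has bottles.
- **Sequence.** Three sections name three sources: the hospital statistician in {16a}, the sponsor and principal investigator team in {16c}, and the uninvolved staff in {17a}.

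**The concern.** A label shared by a group cannot be decoded for one member without being decoded for all who carry it. The labelling in {17a} and the unblinding in {17b} therefore cannot both operate without endangering the blinding promise in {17a}. In a single unit, where the same nursing team hands out the product daily, staff who learn what one code means could apply that to other participants.

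The stake lies mainly outside the DXA measurement. Exposed are the EDE interview, the self-report scales, the effort-dependent items of the fitness battery, and the principal investigator's causality and severity ratings ({22}). Decisions that determine completer status are exposed too. The team withdraws participants for adverse events attributed to the intervention and for dosing deviations ({11b}), and Sample size {14} makes completers the primary evaluation.

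**Working it through.** The plan gives no figure for this point, so there is none to reproduce. The check is a reading of the passages together, then a count of who is exposed.

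**Inputs.** 92 randomised, 46 per arm ({14}); two arms ({8}); 13 weeks of treatment ({8}); 78 weeks of enrolment (Trial status). The number of codes per arm, k, is not stated.

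**Step 1: participants per code.** This is 92/(2k).

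| Codes per arm (assumed) | Participants sharing a code |
|---|---|
| 1 | 92/2 = 46 |
| 2 | 92/4 = 23 |
| 3 | 92/6 = 15.3 |
| 4 | 92/8 = 11.5 |

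With k = 1, the other arm's code follows by elimination, so 46 + 46 = 92 allocations are decodable. With k above 1, elimination no longer decodes every other code. The exposed group shrinks, but it is still more than one person. With a unique number for each participant, one break reveals one allocation.

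**Step 2: who is still open to influence before the end-of-treatment assessment (T1).** Assume even enrolment and no dropout. The number on treatment at once is 92 × 13/78 = 15.3. For a break at week t of enrolment (t from 13 to 78):

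- already past T1: 92 × (t − 13)/78
- on treatment: 15.3
- still to enrol: 92 × (78 − t)/78

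| Break at week | Past T1 | On treatment | Still to enrol | Exposed before T1 |
|---|---|---|---|---|
| 13 | 0 | 15.3 | 76.7 | 92 |
| 39 | 30.7 | 15.3 | 46.0 | 61.3 |
| 78 | 76.7 | 15.3 | 0 | 15.3 |

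These counts are for k = 1. They show that 92 is a ceiling reached only by a break in about the first 13 weeks. A break midway through enrolment leaves about 61 exposed, and one at the end of enrolment about 15.

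**Step 3: how knowledge could spread.** {11c} puts the nurse in contact with each participant's product daily, and {9} places everyone in one department. The Intensive treatment section and Table 2 also have nurses assisting at weighing and attending the weekly review. Under {22}, serious events go to the principal investigator, who rates causality and severity. The article does not say who is told the result of an unblinding, or that the code is printed where nurses see it. Those two links are assumptions.

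**The case against.** The strongest reply is that the article only summarises. {17a} speaks of multiple methods, a full protocol exists, and {16b} mentions a password-protected website that might support participant-level assignment. The phrase group code could also mean the key linking labels to arms. This stands in part: the number of codes and the wording on a sachet are unknown, and silence on code-break mechanics would not by itself be a fault. But the article does not merely stay silent. It states that labelling follows a group code, and it gives the individual ID to the participant only.

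A second reply is that the primary outcome is a machine measurement. That stands for the DXA reading. It does not cover withdrawals that affect completer status, although {20c} also plans an intention-to-treat set, which limits that route.

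Three stronger readings are tempting and unsupported:

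- **That all 92 allocations will be lost.** A break cannot affect T1 assessments already made, and the result would have to reach staff who know other participants' codes.
- **That a break is likely.** The article gives no rate of qualifying events, {17b} makes unblinding permissible and not automatic, and {11b} anticipates no severe harm from the product. A probability built on assumed rates would say little about this trial.
- **That participants could recognise the product and compare codes.** Nothing says that the products differ in taste or tolerance, or that participants see a code. That {16} is silent on sensory matching is not evidence of a difference.

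**Conclusion.** The point holds as a weakness in a stated method. Group-code labelling, combined with permitted unblinding, lets one code break reach beyond the participant concerned. On the assumption of one code per arm, it makes both arms decodable. The practical exposure is about 15 participants on treatment plus all later enrollees, provided that unit staff learn the result and can see the labels. With several codes per arm the exposure is smaller but remains.

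The blinding promise in {17a} is at risk; the documents do not show that it will fail. The outcomes most affected are rated, self-reported or effort-dependent, together with causality ratings and withdrawal decisions. The mismatch between bottles and sachets, and the three accounts of who generates the sequence, are separate inconsistencies that stand without any assumption about codes. The change is worth making because it is cheap and lost blinding cannot be restored.

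**What to change.** 1. In {17a}, replace group-code labelling with a unique kit number for each participant, shown on that participant's boxes and sachets.
2. Hold one code-break record per participant, so that an unblinding under {17b} opens a single allocation.
3. Keep the list linking kit numbers to arms only with the staff uninvolved in the trial. Reconcile {16a} and {16c} with {17a} on who generates and holds the sequence; unique kit numbers protect little if the principal investigator team holds it.
4. Change bottles to sachets/boxes, so that the procedure describes this product.

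The cost is a small one-off relabelling task, with 92 kit numbers in place of group codes, for staff who already label the product. Visits, dosing, assessments and the conditions for unblinding are unchanged.

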### Procedure for unblinding if needed {17b}

Unblinding will be permissible only in the case of a severe adverse event requiring hospitalization or resulting in a fatality.

## Data collection and management

### Plans for assessment and collection of outcomes {18a}

#### Data collection form

The examining physician will complete data collection at the time of enrollment. It includes some general information (marital status, level of education, work activity, family and personal medical history for obesity and related diseases, and drug history) and diagnostic criteria for diagnosing AN according to DSM-5 criteria. All data must precisely reflect the patient’s point of view, that is, be an expression of her knowledge about her and her family’s health.

#### Treatment progress evaluation form

It will include the name of the therapists who conduct the treatment, the date of admission and discharge, the body weight and height measured, and any psychopharmacological therapy.

#### Dropout form

It will report the date of dropout from the treatment and the reasons as described by the patient for the voluntary interruption of therapy.

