### Criteria for discontinuing or modifying allocated interventions {11b}

Patients may withdraw from the trial at any time for any reason. The AmT-P mixture was demonstrated as safe and tolerable at the same dosage and length in malnourished older adults [20]. We do not anticipate that severe harm to require early product discontinuation or medical intervention. However, participants will be withdrawn by the team involved in the trial if they experience any new-onset, moderate, or severe adverse events from the intervention. The trial will be terminated if > 20% of all participants exhibit adverse events of moderate or great severity which are new from baseline or progressively worsening.

No intervention dose modifications or administration frequency changes are allowed. Participants will be considered non-adherent and withdrawn from the trial if deviations from the dosing standard are reported to the study team.

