### Outcomes {12}

#### Primary outcome

Change of LBM with weight regain in patients with AN. The assessment of body composition will be performed at baseline (T0), at the end of the 13 weeks of treatment (T1), and at 24 weeks follow-up (T2) with the dual-energy X-ray absorptiometry (DXA) (Prodigy Primo Lunar, A223040501, General Electric Company, Madison. WI 53,707–7550, USA-EnCORE TM 2009 (v13.31) software). The DXA has been used in previous studies assessing the changes of LBM in patients with AN [27]. The Bioelectrical Impedance (BIA) (Tanita HealthWare® Native Software, Tokyo, Japan) will be used simultaneously to improve body composition measurement accuracy. Indeed, we will measure total body proteins with the method suggested by [28], which associates the DXA with the BIA data, which has good accuracy in evaluating total body water in patients with AN [29].

This primary outcome will be of extreme clinical importance as LBM deficit and abnormalities beyond total body skeletal muscle mass are associated with several severe medical repercussions in other populations, such as low bone mineral density [30], reduction in physical fitness (i.e., strength, metabolic function, and athletic performance) [31], more extended hospitalization [32], and high rates of mortality [33].

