### Methods in analysis to handle protocol non-adherence and any statistical methods to handle missing data {20c}

We will test superiority using two analysis sets; the intention-to-treat set, considering all patients as randomized regardless of whether they received the randomized treatment, and the “per protocol” analysis set. Criteria for determining the “per protocol” group assignment will be established by Data Manager before the trial begins.

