#### Imputation procedure for missing data

We will report reasons for withdrawal for each randomization group and compare the reasons qualitatively. Any missing data’s effect on results will be assessed via sensitivity analysis of augmented data sets. Dropouts will be included in the analysis by modern imputation methods for missing data.

The main feature of the approach is creating a set of clinically reasonable imputations for the respective outcome for each dropout. This will be accomplished using a set of repeated imputations created by predictive models based on the majority of participants with complete data. The imputation models will reflect uncertainty in the modeling process and inherent variability in patient outcomes, as reflected in the complete data.

After the imputations are completed, all of the data (complete and imputed) will be combined, and the analysis performed for each imputed-and-completed dataset. Rubin’s multiple (i.e., repeated) imputation method will be used to estimate the treatment effect. We propose to use 15 datasets (an odd number to allow use of one of the datasets to represent the median analytic result).

These methods are preferable to simple mean imputation, or simple “best–worst” or “worst-worst” imputation, because the categorization of patients into clinically meaningful subgroups, and the imputation of their missing data by appropriately different models, accords well with best clinical judgment concerning the likely outcomes of the dropouts, and therefore will enhance the trial’s results.

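### Patients who stop the product or are withdrawn have no stated week-13 LBM assessment, so the intention-to-treat analysis is a weak check on the primary completer analysis

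*Protocol article*

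**What the plan says.** **Measurement.** The Primary outcome section places DXA at baseline, "at the end of the 13 weeks of treatment (T1), and at 24 weeks follow-up (T2"). The readable text names no DXA between T0 and T1 and none at early exit.

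**Withdrawal.** Section {11b} says that "participants will be withdrawn by the team involved in the trial if they experience any new-onset, moderate, or severe adverse events from the intervention". It then says that patients with reported dosing deviations count as non-adherent and leave the trial.

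**What is recorded.** The Dropout form is described in one sentence: "It will report the date of dropout from the treatment and the reasons as described by the patient for the voluntary interruption of therapy". Separately, the Treatment progress evaluation form holds body weight and the discharge date, and Table 2 lists weekly weighing. Section {18b} promises every effort to obtain assessments, with flexible and split sessions. It gives no rule for patients who have stopped.

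**Analysis.** Sample size {14} makes the completer analysis the main evaluation. Section {20c} adds a per-protocol set and an intention-to-treat set, the latter "considering all patients as randomized regardless of whether they received the randomized treatment". Dropouts enter by multiple imputation from "predictive models based on the majority of participants with complete data".

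**The concern.** An intention-to-treat analysis needs the outcome of patients who did not take the product as planned. Section {11b} withdraws those same patients, and nothing readable says that their T1 assessment still takes place. If it does not, a patient who stops at week 5 or week 10 has only a baseline LBM up to T1. Both the mixed model and the imputation must then take her change from other patients, under a missing-at-random assumption.

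That assumption is doubtful here. Withdrawal is triggered partly by events attributed to the product, so it can differ by arm, and early leavers have had less time to regain weight and LBM. Because the completer analysis is primary, the intention-to-treat analysis is the main protection against selective loss. If it is filled from completers, it will tend to repeat the completer result. An analysis plan cannot repair this later, because a scan that was not taken cannot be recovered.

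**Working it through.** **Inputs, all from Sample size {14}.** "the control group could have an 8.8% increase in LBM"; "the intervention group could have a further 2% increase in LBM", which gives 10.8%; "The standard deviation assumed for the sample size calculation is 3.2" (per cent); 80 completers; 15% interruption; 92 randomised, 46 per arm. Alpha and power are not stated with the calculation. Two-sided 0.05 and 80% are assumed.

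**1. The plan's own figure.** n per arm = 2 × (1.96 + 0.842)² × 3.2² / 2² = 40.2, rounded up to 41. The stated 40 per arm has 79.8% power, so 80 completers is reproduced to within two patients. The 92 is 80 × 1.15.

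**2. Patients who could be affected.** 0.15 × 92 = 13.8, about 14 in all and about 7 per arm (0.15 × 46 = 6.9). This is an upper figure under the stated rate, because the 15% describes interruption of the intervention and not missing DXA.

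**3. Completer difference against the all-randomised difference.** Assumption: at week 13, leavers have half the completers' gain, that is 5.4% on active and 4.4% on placebo. Imputation that gives leavers the completer mean of their own arm returns 10.8 − 8.8 = 2.0 in every row.

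| Loss, active / placebo (assumed split) | Active mean | Placebo mean | Difference |
|---|---|---|---|
| 15% / 15% | 0.925 × 10.8 = 9.99 | 0.925 × 8.8 = 8.14 | 1.85 |
| 20% / 10% | 0.8 × 10.8 + 0.2 × 5.4 = 9.72 | 0.9 × 8.8 + 0.1 × 4.4 = 8.36 | 1.36 |
| 10% / 20% | 0.9 × 10.8 + 0.1 × 5.4 = 10.26 | 0.8 × 8.8 + 0.2 × 4.4 = 7.92 | 2.34 |

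The direction of the error depends on which arm loses more.

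**4. How wrong the imputation must be to matter.** With 15% imputed in each arm, an error of 1 point in the mean imputed gain of one arm's leavers moves the difference by 0.15. At 39 per arm (92 × 0.85 = 78.2 completers), SE = 3.2 × √(2/39) = 0.725 and the critical difference is 1.96 × 0.725 = 1.42. An observed 2.0 loses significance when active-arm leavers do (2.0 − 1.42) / 0.15 = about 3.9 points worse than imputed. Under the half-gain assumption the overstatement on active is 10.8 − 5.4 = 5.4 points, but the placebo leavers are overstated by 4.4 points as well. The two largely cancel when loss is equal.

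**5. If all 46 per arm were scanned at week 13.** SE = 3.2 × √(2/46) = 0.667, and power = Φ(difference / 0.667 − 1.96). This gives 85.0% for a difference of 2.00 (stoppers keep the full 2-point benefit), 79.2% for 1.85 (they keep half) and 72.2% for 1.70 (they keep none). The SD is held at 3.2, which is an assumption.

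**The case against.** The strongest reply is that this is silence in a condensed article. The dropout sentence describes a form, and one limited to voluntary interruption. Table 3 and Fig. 1 cannot be read here and may contain an exit visit. A fuller protocol exists. The adverse-event sentence stands under a heading about the allocated intervention and does not say that the patient leaves the trial. Only the dosing-deviation sentence does.

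Much of this stands. A reader might infer that no outcome at all is measured once a patient stops, and that the intention-to-treat result for stoppers comes from the model alone. The documents do not support that:

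- Weight regain is a secondary outcome, weighing is weekly, and weight is on the progress form. The gap concerns LBM and other measures taken only at T0 and T1.
- Imputation could draw on baseline LBM and recorded weights. The imputation section also foresees different models for clinically meaningful subgroups and a sensitivity analysis.
- The 15% cannot be read as 15% without a T1 scan.
- The 1.36 is one assumed scenario. Reversing the split gives 2.34.

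What the reply does not remove is the conflict in the text itself. Taking a patient out of the trial for a dosing deviation cannot be squared with analysing everyone regardless of treatment received, unless assessments continue, and nothing readable says that they do. The general promise of effort in {18b} does not override {11b}. Whatever subgroup models are used, their stated source is still participants with complete data.

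**Conclusion.** The point holds as a conflict between {11b}, {18b} and {20c} that leaves observed T1 LBM unsecured for the patients on whom the intention-to-treat analysis depends. It does not show that assessments do stop, or that the result will be biased in a known direction.

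Up to about 14 of 92 patients could be affected. If leavers gain half as much as completers, the gap between the completer and the all-randomised difference is 2.0 − 1.85 = 0.15 points with equal 15% loss. With losses of 20% and 10% it is 2.0 − 1.36 = 0.64 points too high or 2.34 − 2.0 = 0.34 points too low, depending on the arm. The half gain and the unequal loss rates are assumptions with no source in the document. The matter should be settled while T1 scans can still be taken. Confidence is medium, because the schedule table and flow chart are not readable.

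**What to change.** Reconcile {11b}, {18b} and {20c} by separating the end of product intake from the end of assessments:

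1. State that stopping the product, for any reason, does not end trial assessments. Take the planned T1 set, including DXA, at week 13 for every consenting randomised patient, and use these values in the intention-to-treat analysis. This is practicable: there is one site, the programme lasts 13 weeks, and Recruitment {15} says that leaving the study does not affect later treatment. A patient off the product may therefore still be on the unit.
2. For a patient who leaves the programme early, attempt DXA, BIA and weight on the discharge day, and add the date and results to the dropout form. Enter them by actual time since T0 in the mixed model and the imputation. Actiheart cannot be included, because it is worn for four consecutive days.

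No change to when the product is stopped is proposed.

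The first item costs protocol wording and scans that were already planned. The second costs form fields and some scheduling at discharge. Some leavers will refuse. An early scan is not a week-13 value, so its use still rests on a model of the time course, although with more information than baseline alone.
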